## **12.2 Data variables collected**

Data to be collected will include:

### **1. Screening**

- Patient identifier(s)
- Inclusion and exclusion criteria
- Reason for non-enrolment

### **2. Baseline (immediately prior to randomisation)**

- Baseline demographics (age, sex, weight, ethnicity)
- Suspected source of infection
- Usual residence
- Pre-existing comorbidities (as defined by the Charlson Comorbidity Index Score)
- Physiological and laboratory variables, if available
- Date, time and name of first IV antimicrobial agent
- IV fluids administered prior to randomisation (volume and type)
- Severity of illness and organ failure scores (APACHE II, SOFA)

### **3. During delivery of the intervention (up to 24 hrs)**

- Physiological and laboratory variables, if available
- Type and volume of IV fluids
- Type and dose of vasoactive agents

### **4. Other data**

- Daily fluid balance until day 7 post-randomisation or ICU discharge whichever occurs first
- Source of infection and microbial culture results
- Type and timing of IV antimicrobials
- Type and timing of co-interventions e.g. source control procedure, corticosteroids, extracorporeal membrane oxygenation
- CVC insertion date and time
- Complication outcomes (CVC complications, APO, ischaemic events)
- Date and time consent granted or the date the study brochure presented
- Treatment limitations or withdrawal
- Patient clinical costings for index admission

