## **Significance**

On the basis of the existing evidence, there is equipoise about the effect of a fluid-restricted and early vasopressor strategy compared to a more liberal fluids and later introduction of vasopressors strategy on sepsis mortality and on longer term functional outcome among survivors. In addition, the organisational and resource implications for acute health systems of these approaches are unknown. The ARISE FLUIDS trial will address an important gap in the evidence base regarding the early haemodynamic management of patients with septic shock, provide clear guidance for bedside clinicians and optimise important patient-centred outcomes.

If it can be demonstrated that a volume-sparing approach increases the number of days-alive out of hospital, the potential impact on global resource use in the healthcare system will be substantial. We will undertake a detailed economic evaluation and follow patients up to assess their functional outcome at 12 months, a time frame which is relevant for consumers and supported by literature. The collaboration between researchers in the ANZICS CTG and the ACEM CTN will be further strengthened. Harmonisation with collaborative trials overseas will place Australia and New Zealand in the vanguard of a worldwide research effort to reduce the human and economic burdens of this World Health Organisation Global Health Priority disease.

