### 8.3 Tertiary outcomes

1. Incidence and duration of invasive mechanical ventilation
2. Incidence and duration of vasopressor support
3. Incidence and duration of acute renal replacement therapy
4. ED length of stay
5. ICU length of stay
6. Hospital length of stay
7. In hospital mortality (censored at 90 days)

8. Mortality at 6 and 12 months\*
9. Quality of life at 6 and 12 months\*
10. Cost-effectiveness measured as cost/QALY\*

\*May be reported separately when 12-month follow up complete

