### **10.9 Follow up at day 90, 6 and 12 months**

The descriptor for the person who is legally allowed to give consent will vary between jurisdictions. For the purposes of this protocol, the descriptor 'legally authorised representative' (LAR) describes the person who is legally allowed to give consent for the participant.

The participant or a LAR, if the participant has not regained capacity, will be contacted via a telephone call at 90 days, 6 and 12 months after randomisation for study follow up.

The day 90 follow up will be to establish survival at this time point and additionally to collect important information on readmissions and discharge to other hospitals, rehabilitation hospitals or long term nursing care facilities. This will inform the primary outcome for the study. As this information will be collected from the participant or (LAR), a diary/information collection sheet will be provided prior to hospital discharge to assist with this information collection.

At 6 and 12 months after randomisation, the participant or LAR will be contacted again via a phone call. This call will collect information quality of life and functional outcome information by the E-Q-5D and WHODAS 2.0 surveys.

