## 6. Outcome data

- Date/s and time of initiation and cessation of invasive ventilation
- Date/s and time of initiation and cessation of vasopressor support
- Date/s and time of initiation and cessation of acute renal replacement therapy
- Vital status at ICU, hospital discharge, day 28, day 90, 6 months and 12 months post-randomisation
- ED, ICU and hospital admission and discharge dates and times, including readmissions
- ED, ICU and hospital discharge destination
- Cause-specific hospital mortality
- Rehabilitation and residential care admission and discharge dates
- Functional status at 6- and 12-months post-randomisation (as measured by the WHODAS)
- Quality of life at 6- and 12-months post-randomisation (measured using the EQ-5D-5L)

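### Cost per QALY has no stated horizon although it is tied to 12-month follow-up; resource use is asked about explicitly only at day 90, and utility is first measured at month 6

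*Protocol*

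**What the plan says.** **Outcome.** Protocol Section 8.3 lists "Cost-effectiveness measured as cost/QALY" as tertiary outcome 10. It carries an asterisk whose note reads "May be reported separately when 12-month follow up complete". The Significance part of Section 6 states: "We will undertake a detailed economic evaluation and follow patients up to assess their functional outcome at 12 months". Neither place gives a time horizon for the cost/QALY itself.

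**Costs and resource use.** In Section 12.2, the only item labelled as a cost is "Patient clinical costings for index admission" (under Other data). The Outcome data list adds "ED, ICU and hospital admission and discharge dates and times, including readmissions" and "Rehabilitation and residential care admission and discharge dates". Neither of these two items has an end date.

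**Contacts.** Section 10.9 assigns questions on readmission, transfer to other hospitals, rehabilitation and nursing care to the day-90 contact, where they inform the primary outcome. A diary is handed out before discharge to support that contact. Of the 6- and 12-month contacts it says: "This call will collect information quality of life and functional outcome information by the E-Q-5D and WHODAS 2.0 surveys". Section 12.1 describes those later contacts in the same way.

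**Utility.** Section 12.2 lists EQ-5D-5L at 6 and 12 months only. Neither the baseline list nor the description of the day-90 contact includes a utility measure.

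**The concern.** A cost/QALY needs costs and QALYs counted over the same period. If the evaluation runs to 12 months, the protocol shows a survival and utility side that reaches 12 months, but no resource-use question after day 90. Patients who survive because of the better strategy would then add QALYs up to month 12, while their later readmissions and care would not be counted. That flatters the arm with better survival.

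The second issue concerns measurement. The hypothesis in Section 7.2 is a gain in days alive and out of hospital by day 90. Any difference in quality of life in that window falls before the first utility measurement and would have to be assumed.

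An analysis plan can choose unit costs and interpolation rules. It cannot recover answers that nobody asked for. Section 12.1 restricts collection to necessary variables, and the protocol names no data linkage that would fill the gap.

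**Working it through.** The protocol gives no figure for the economic outcome, so there is none to reproduce. The check sets the data lists against the outcome and then illustrates size.

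**1. Coverage by period, as the protocol describes the contacts**

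| Period | Resource use | Utility |
|---|---|---|
| Index stay | Costed; dates listed | None |
| Discharge to day 90 | Dates listed and asked about at day 90; no costing item | None |
| Day 91 to month 6 | Dates listed without end date; no question in the calls | EQ-5D-5L at month 6 |
| Months 6 to 12 | As above | EQ-5D-5L at month 12 |

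Vital status is recorded at ICU and hospital discharge, day 28, day 90, 6 months and 12 months (Section 12.2), so the survival part of the QALY is covered throughout.

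**2. Share of a 12-month horizon without resource-use data**

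Assumptions: the horizon is 365 days, and collection stops at the day-90 contact.

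365 − 90 = 275 days; 275/365 = 0.753, about 75%.

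**3. Illustration of the cost effect (no input below comes from the protocol)**

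Assume an uncounted later cost of $2,000 to $8,000 per survivor, 5 percentage points better survival, and 0.6 QALY per extra survivor, with no other QALY difference.

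- Incremental cost missed per patient: 0.05 × $2,000 = $100, up to 0.05 × $8,000 = $400.
- QALY gain per patient: 0.05 × 0.6 = 0.03.
- Understatement per QALY: $100/0.03 ≈ $3,300, up to $400/0.03 ≈ $13,300.

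The survival difference cancels from the last line: $2,000/0.6 and $8,000/0.6 give the same results. The ratio depends only on the assumed later cost and the assumed QALYs per extra survivor.

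**4. Illustration of the utility effect (assumed values)**

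Take a 12-month survivor with utility u at both 6 and 12 months and starting utility u0, joined by straight lines.

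- QALYs in months 0–6: 0.5 × (u0 + u)/2.
- With u = 0.7: 0.175 if u0 = 0, and 0.350 if u0 = 0.7.
- QALYs in months 6–12: 0.5 × 0.7 = 0.350.
- 12-month total: 0.525 to 0.700. The first half-year makes up 33% (0.175/0.525) to 50% (0.350/0.700), depending only on the assumed starting value.

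Now suppose a day-90 utility v had been measured, with u0 = 0 and u = 0.7. Months 0–6 become 0.25 × (0 + v)/2 + 0.25 × (v + 0.7)/2 = 0.25v + 0.0875.

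- v = 0.3: 0.1625
- v = 0.5: 0.2125
- v = 0.65: 0.250

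Without a day-90 value, all three patients would be given 0.175. If survivors in one arm were at 0.65 and in the other at 0.5 on day 90, a difference of 0.250 − 0.2125 = 0.0375 QALY per survivor would be recorded as zero.

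**The case against.** **Dates can be costed.** A reader might infer from the costing item that readmissions count for nothing in the economic analysis, or that costs stop at index discharge. The documents do not support that. Dates for readmission, rehabilitation and residential care are listed, dated bed-days are resource-use data, and valuing them with unit costs is an analysis step that an unseen plan may contain. What stands is narrower: no costing item is listed beyond the index stay, and the questions are assigned explicitly only to day 90.

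**The horizon is not stated.** In the Significance text, the 12 months attach to functional outcome, and the asterisk concerns reporting. A 12-month cost/QALY is implied, not fixed. The 75% figure is therefore conditional, also because the date items have no end date. This objection stands, and it is itself a reason to state the horizon.

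**Late EQ-5D does not shorten the QALY period.** A reader might infer that, with no utility before month 6, costs and QALYs cover different periods. That does not follow: vital status is tracked from the start and a starting utility can be assumed. The result is a measurement gap. A patient-reported baseline is also hardly feasible, given Section 11.5.2 on patients' inability to consent at enrolment. That is no obstacle at day 90, when a call is already made.

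**The sizes are illustrative.** The 0.6 QALY per extra survivor does not match the 0.525 that the straight-line curve from 0 gives. The 0.163 to 0.250 range (working, step 4) is a level per survivor and largely cancels if recovery is similar in both arms. The $100 to $400 per patient is about 0.3% to 1% of the $39,000 cost per sepsis episode in Section 6. No willingness-to-pay threshold is given, so no changed conclusion is shown. All of this stands.

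**Conclusion.** The point holds in a limited form. The protocol ties cost/QALY to completed 12-month follow-up without fixing its horizon, lists costings for the index admission only, and asks about later resource use explicitly only at day 90. On two conditions, a 12-month horizon and collection as Section 10.9 describes it, about 275 of 365 days lack resource-use data, and the bias favours the arm with better survival. Separately, utility over the first six months is unmeasured, including the 90-day window of the hypothesis.

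The dollar and QALY figures show direction and possible order of size under assumed inputs. They are not estimates for this trial. Severity is low: the outcome is tertiary, may be reported separately, and does not affect the primary outcome, the secondary outcomes, the sample size or safety. The change is worth making because it is cheap and because data missed at a call are hard to recover later.

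**What to change.** 1. In Section 8.3, state one horizon that applies to both costs and QALYs.
2. In Section 12.2, extend the costing item from the index admission to readmissions, rehabilitation and residential care, valuing the dates already listed with standard unit costs. Give those date items an end date that matches the horizon.
3. If the horizon is 12 months, add the day-90 readmission and care questions, in short form, to the existing 6- and 12-month calls in Sections 10.9 and 12.1.
4. Add EQ-5D-5L to the existing day-90 call.

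If item 3 is not adopted, restrict tertiary outcome 10 to the period that the resource data cover. Item 4 then matters more, because a 90-day horizon would otherwise contain no measured utility at all.

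Cost: a few questions on calls already planned, one more EQ-5D-5L per survivor, and unit-cost work. The downside is slightly longer calls and some recall error over the longer intervals. No new visits are needed.

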### **5. Adverse events**

See section 13 below

## 6. Outcome data

- Date/s and time of initiation and cessation of invasive ventilation
- Date/s and time of initiation and cessation of vasopressor support
- Date/s and time of initiation and cessation of acute renal replacement therapy
- Vital status at ICU, hospital discharge, day 28, day 90, 6 months and 12 months post-randomisation
- ED, ICU and hospital admission and discharge dates and times, including readmissions
- ED, ICU and hospital discharge destination
- Cause-specific hospital mortality
- Rehabilitation and residential care admission and discharge dates
- Functional status at 6- and 12-months post-randomisation (as measured by the WHODAS)
- Quality of life at 6- and 12-months post-randomisation (measured using the EQ-5D-5L)

## 12.3. Monitoring

Prior to study commencement, a start-up meeting will be held for all study staff. During the study, onsite [or remote as appropriate] and central monitoring will be conducted by the project manager or a delegated coordinating centre representative. A minimum of one monitoring and one close-out visit per site will occur. The purpose of these visits is to ensure the study is conducted according to the protocol, all applicable guidelines and regulations, and to perform source data verification.

Medical records, any other relevant source documents and the site investigator files must be made available to the monitor for these monitoring visits during the course of the study and at the completion of the study as needed.

A monitoring report will be prepared following each visit and reviewed by the management committee. A copy of the report will be sent to the principal investigator and study coordinator at the site and will be filed in the site investigator file.

The aims of monitoring visits are to:

- Check the accuracy of the data base by performing source data verification of the electronic CRF against the original source documents.
- Check for protocol deviations and report these to the chief investigator as necessary.
- Review outcome data for each monitored participant.
- Confirm the consent procedures approved by the site's HREC have been followed.
- Check data security and access.
- Review all serious adverse events (SAEs) and follow up all reported SAEs.
- Review investigator site files for completeness and accuracy.
- Assist the study staff with any queries or problems they may have in relation to the study.

## **12.4 Protocol deviations**

A protocol deviation is an unanticipated or unintentional departure from the expected conduct of an approved trial that is not consistent with the current research protocol or consent document. A protocol deviation may be an omission, an error, addition or change in any procedure described in the protocol. If any ineligible participants are enrolled, as the study is intention to treat, these will be recorded as protocol deviations. Protocol deviations and rates of protocol deviations may be indicative of non-compliance with the protocol and will be regularly reported to the management committee. Reports on protocol deviations may trigger specific site contact and feedback and additional monitoring requirements/visits.

Given that the investigator is responsible for patient safety and care, he/she may implement a deviation from the protocol to eliminate an immediate hazard to trial participants without HREC approval. All protocol deviations must be reported via the trial database to the coordinating centre. The relevant HREC will be notified of protocol deviations or serious breaches in accordance with the NHMRC framework according to each HREC's requirements.

## **13. STATISTICAL CONSIDERATIONS**

Participants who do not receive the allocated intervention according to the parameters set in the allocated study arm will be analysed according to the allocated arm according to the intention to treat principle.

### **13.1 Sample size calculation**

Based on the data from the ARISE trial [10], the mean (standard deviation) of DAOH-D90 was 60(31). Assuming a clinically important increase of 7 days in the vasopressors arm, a sample size of 950 will have 90% power to detect this difference with a type I error rate of 0.05 (including a 15% inflation factor to account for the non-parametric distribution). Allowing for a 5% drop out rate, we will recruit 1000 participants to the trial. A 7 day difference in DAOH-D90 is considered clinically important and is supported by consumers.

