## 8. STUDY OUTCOME MEASURES

### 8.1 Primary outcome

The primary study outcome is the number of days alive out of hospital at 90 days post randomisation (DAOH-D 90). Participants who die on or prior to day 90 will be assigned zero days alive and out of hospital.

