### **13.2 Statistical and analytical plan**

The primary outcome (DAOH-D90) and other non-parametric outcomes will be analysed using quantile regression with results presented as median difference (95%CI). Mortality and other binomial outcomes will be analysed using logistic regression with results reported as odds ratios (95%CI). Time to event outcomes will be analysed using proportional hazards regression with results presented as Kaplan Meier or cumulative incidence curves where mortality is a competing risk. Functional status and quality of life will employ longitudinal analysis techniques to account for data collected at both 6 and 12 months. All analyses will account for site with participants nested within site and site treated as a random effect. Where baseline imbalance ( $p < 0.2$ ) is observed between treatment arms, sensitivity analysis will be performed adjusting for imbalanced variables. Sensitivity to missingness will be performed using multiple imputation. A secondary analysis will be conducted using a Bayesian approach to model a posterior probability of the odds ratio for days alive and out of hospital at 90

days post-randomisation between the intervention and control group with associated 95% credible interval (CrI). Statistical analysis will be performed using SAS or R and a detailed statistical analysis plan will be published or posted in the public domain prior to study completion.

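### The stated 90% power is for a difference in means; the power of the planned median comparison is not given, and it depends strongly on how the treatment works

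*Protocol*

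**What the plan says.** Protocol section 13.1 takes a mean DAOH-D90 of 60 days with standard deviation 31 from the ARISE trial, "Assuming a clinically important increase of 7 days in the vasopressors arm", and concludes that "a sample size of 950 will have 90% power to detect this difference with a type I error rate of 0.05". It adds that this is "including a 15% inflation factor to account for the non-parametric distribution". It then continues: "Allowing for a 5% drop out rate, we will recruit 1000 participants to the trial".

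Section 13.2 says that the primary outcome "will be analysed using quantile regression with results presented as median difference (95%CI".

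Section 8.1 defines how death enters the outcome: "Participants who die on or prior to day 90 will be assigned zero days alive and out of hospital".

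The protocol gives no control-arm median, no expected difference in medians, no outcome distribution and no power calculation for the quantile regression. Neither section 13.1 nor the passage on the primary outcome in section 6 says whether the 7 days is a difference in means or in medians.

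**The concern.** A mean and a median of this outcome can respond very differently to the same treatment effect. Deaths form a block of zeros far below the median. Moving a patient from zero to some 70 days adds a lot to the mean, but shifts the median only slightly. Shortening survivors' hospital stay acts on the part of the distribution where the median lies. One 7-day gain in the mean can therefore be a small or a large gain in the median.

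The 15% allowance does not bridge this gap. It is close to the worst-case allowance for a rank-sum test (1/0.864 = 1.157), but the planned test compares medians.

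The stated power is what readers will use to interpret a null result. If a 7-day mean benefit arose through survival, the primary analysis could well miss it, and the result might still be read as evidence against an effect of the planned size. An observed median difference would also be judged against 7 days without the protocol having said on which scale that threshold was set.

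**Working it through.** **Inputs from the protocol.** Mean 60, SD 31, difference 7, power 90%, type I error 0.05, inflation 15%, dropout 5% (section 13.1); 1:1 allocation (section 10.1); death by day 90 scored zero (section 8.1). Two-sided testing is assumed, because it reproduces the stated figure.

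**Step 1: the protocol's own figure.** For two means, n per arm = 2(1.960 + 1.282)² × 31²/7² ≈ 412.1, or 413 with the t correction, giving 826 in total. Then 826 × 1.15 = 949.9, so 950, and 950/0.95 = 1000. The stated size is exactly that of a comparison of means plus the two allowances.

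**Step 2: what mean 60 and SD 31 allow.** The second moment is 60² + 31² = 4561. With a proportion m at zero, survivors have mean 60/(1 − m) and second moment 4561/(1 − m). Their variance cannot be negative, so 1 − m ≥ 3600/4561 = 0.789. Control mortality is at most about 21%.

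**Step 3: a gain through deaths only.** If survivors are unchanged, raising the mean from 60 to 67 needs 1 − m₁ = (67/60)(1 − m):

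- m = 19%: m₁ = 9.6%
- m = 15%: m₁ = 5.1%
- m = 12%: m₁ = 1.7%
- m below 1 − 60/67 = 10.4%: impossible

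The proportion of patients above the control median rises from 50% to 50% × 67/60 = 55.8%, whatever the mortality or survivor shape. This is why the power in this scenario hardly varies.

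**Step 4: large-sample power of the median comparison.** With f the outcome density at each arm's median, SE² = (1/f₀² + 1/f₁²)/(4 × 475). At 19% mortality with beta-distributed survivors (mean 74.1, SD 12.0), the median moves from 72.9 to 75.1. The difference is 2.22 and the SE 1.32, so power = Φ(2.22/1.32 − 1.96) ≈ 39%.

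**Step 5: simulation.** The setting is 475 per arm, whole days and a Wald test with bootstrap SE. Survivors follow a scaled beta, or 90 minus a gamma, calibrated to mean 60 and SD 31. The true mean difference is 7 days throughout. Ranges span the two survivor shapes.

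| Mechanism | Control mortality | Median shift (days) | Power, median | Power, means |
|---|---|---|---|---|
| Deaths only | 15% (to 5.1%) | 2.7–3.5 | 32–36% | 97% |
| Deaths only | 19% (to 9.6%) | 2.0–2.2 | 34–36% | 97–98% |
| Deaths only | 20% (to 10.7%) | 1.5–1.6 | 33–35% | 97–98% |
| Half and half | 10% (to 4.8%) | 4.3–4.8 | 46–68% | 97–98% |
| Half and half | 15% (to 10%) | 4.5–5.1 | 68–80% | 95–97% |
| Half and half | 20% (to 15.3%) | 5.0–5.2 | 100% | 95–96% |
| Hospital days only | 10% | 5.7–5.9 | 62–94% | 93–94% |
| Hospital days only | 15% | 7.3–7.9 | 98–100% | 94–95% |
| Hospital days only | 20% | 9.3–9.6 | 100% | 92–93% |

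A separate run of the hospital-days-only case with beta survivors went down to 44% at the lower end of an 8% to 19% mortality range. A rank-sum test on the deaths-only data had 70% to 75% power. With no treatment effect the median test rejected 6.6% of the time, so its low power is not due to a conservative test.

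**Illustration only.** For normal data a median comparison needs π/2 times the patients: 2 × 412.1 × π/2 ≈ 1,295. With 950, power is about 79%. DAOH-D90 is bounded, skewed and has a spike at zero, so these figures do not describe it.

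**The case against.** A reader might infer that the trial really has only about 30% power. The documents do not support that. About one third is the low corner of the range. It requires the whole gain to come from deaths, with mortality roughly halved at 19% and cut by about two thirds at 15%. Nothing in the protocol says the 7 days arise that way. Section 6 says the outcome captures death and morbidity together, and the pilot it describes reports shorter vasopressor support. The same section gives 8% in-hospital mortality in an observational septic shock cohort (n=82), a level at which a deaths-only 7-day mean gain is impossible; registry data there give 22% with shock. In the deaths-only corner, the 90-day mortality secondary outcome would detect a fall from 19.0% to 9.6% with about 99% power, although the primary result could still be null.

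The 7 days may also have been meant as a median difference. With beta survivors and the control density at the median in both arms, large-sample power is then about 60% to 71% at 8% to 12% mortality, 83% at 15%, 94% at 17% and over 99% at 19%. The stated 90% can therefore be too high or too low.

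A reader might further infer that the primary analysis must change to the mean, or that the secondary Bayesian odds ratio is an error. Neither follows. A median is a defensible summary of a skewed outcome, and a secondary analysis may use another scale. The 15% allowance is openly stated and the arithmetic is right.

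What stands is that the protocol fixes both a power figure and a primary analysis, and they concern different quantities. This is not detail left to a later analysis plan.

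**Conclusion.** The concern holds in this form: the 90% in section 13.1 is not a property of the test in section 13.2, and the 15% allowance does not make it one. For a true 7-day gain in the mean, the planned median test has power from about one third to near 100%, depending on mechanism, control mortality and survivor shape. A comparison of means has 92% or more in every scenario tabulated.

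The range rests on assumptions that the protocol does not supply: control mortality of 8% to 20%, beta or gamma survivor shapes, and how the gain divides between deaths and hospital days. Site effects and the interim analysis were not modelled. No single value in the range should be quoted as the trial's power.

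**What to change.** In section 13.1, replace the 90% with the simulated power of the planned median comparison at 950 evaluable patients. State the assumed control distribution (including mortality and the median), whether the 7 days is a mean or a median difference, and the range of power across gains through deaths, hospital days and both.

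Alternatively, say plainly in section 13.1 that the 90% applies to a comparison of means, and add to section 13.2 the mean difference in DAOH-D90, with a bootstrap or robust 95% CI, as a prespecified supportive analysis.

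Making the mean the primary estimand is open to the sponsor but is not a required correction. It would change the primary analysis of a trial with a planned interim analysis, which is more than a rewording.

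The first option costs a short simulation and a revised paragraph; the second costs wording and one supportive analysis. Neither needs more patients.
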